## Abstract

Global infection and mortality rates from severe acute respiratory syndrome coronavirus-2 (SARS-CoV-2) are disproportionately high in certain populations, including amongst older people. Care home residents are frequently exposed to infection due to contact with staff and other residents, and are highly susceptible to infection due to their age and co-morbidity. In England, official statistics suggest that at least 25% of all deaths in care home residents since the start of pandemic are linked to coronavirus disease 2019 (COVID-19), but limited testing for SARS-CoV-2 early in the pandemic means estimates of the true burden of disease are lacking. Additionally, little is known about patterns of transmission between care homes, the community and hospitals, or the relationship between infection and immunity in care home staff and residents. The VIVALDI study plans to address these questions.

VIVALDI is a prospective cohort study aiming to recruit  6,500 staff and 5000 residents from 105 care homes across England. Successive rounds of testing for infection will be performed over a period of 12 months.  Nasopharyngeal swabs will detect evidence of viral RNA and therefore active infection (accompanied by collection of data on symptoms), whereas blood tests will detect antibodies and evidence of cellular immunity to SARS-CoV-2. Whole genome sequencing of viral isolates to investigate pathways of transmission of infection is planned in collaboration with the COVID-19 Genomics UK Consortium. Qualitative interviews with care home staff will investigate the impact of the pandemic on ways of working and how test results influence infection control practices and behaviours. Data from residents and staff will be linked to national datasets on hospital admissions, antibody and PCR test results, mortality and care home characteristics.

Data generated will support national public health efforts to prevent transmission of COVID-19 and protect care home staff and residents from infection.

**Protocol registration**:
ISRCTN14447421 05/06/2020

## Introduction

Severe acute respiratory syndrome coronavirus 2 (SARS-CoV-2) has caused a large number of deaths worldwide and rapidly changed how people live their lives by restricting social contact and daily activities. Early evidence pointed to the disproportionate impact of coronavirus disease 2019 (COVID-19) on older people, ethnic minorities and people with co-morbidities
^1,
2^. Care home residents have underlying risk factors for severe outcomes (age, comorbidity), but are also likely to have high rates of exposure to infection, through contact with care home staff or other residents. Studies from the USA, Canada and Europe have consistently shown high prevalence of SARS-CoV-2 in care home residents and staff, associated with significant mortality in residents
^3–
5^.

In England an estimated 450,000 individuals aged > 65 years live in approximately 9,000 care homes
^6^. Mortality data from the Office of National Statistics (ONS) suggests that >45,000 care home residents have died during the pandemic, although only 12,500 of these deaths were explicitly linked to COVID-19
^7^. Accurate estimates of the burden of SARS-CoV-2 infection in care home residents and staff and the proportion of cases without symptoms are lacking because there has to date been limited testing for infection (antibody and RNA tests), and there is no comprehensive surveillance system for infection in care homes. We also have little insight into how infection transmits in the care home, both between staff and residents, and between care homes and other settings (community, hospitals), or how the pandemic has impacted on ways of working in the care home. The prevalence and duration of immunity to SARS-CoV-2 among staff and residents is also unknown.

The Department of Health & Social Care is currently rolling out infection (PCR) testing to all care home staff and residents
^8^. This will provide accurate data on the prevalence of infection across all care homes and insights into the types of care homes that are most likely to develop outbreaks. But this large-scale approach is not well-suited to assessing how outbreaks progress over time, or duration of immunity – information that is essential to inform the approach to testing in care homes for current and future pandemic waves. 

These questions can be answered most efficiently through a large prospective cohort study of care home staff and residents with repeat testing for infection and analysis of the immune response (antibody and cellular immunity). This will be combined with detailed data collection on symptoms and risk factors for infection, and linkage to NHS and public health data sources including viral sequencing. Through linkage to an existing study (
CATCH-19), we will also undertake qualitative interviews with 30 healthcare workers in a subset of care homes to gain insights into how the pandemic has impacted on healthcare staff and ways of working in the care home. This study is one of the largest undertaken in care homes, and will inform planning and the national public health response to COVID-19

This VIVALDI-2 study will be performed in conjunction with the VIVALDI-1 study. VIVALDI-1 is a cross-sectional survey of all 9000 care homes in England which provide dementia care or care to residents aged >65 years. The study is a collaboration between the ONS, Public Health England and UCL. The survey was delivered to care home managers and collected information on care home characteristics and staffing (number and type of staff, number of residents, sickness pay, use of agency staff), disease control measures (cohorting, isolation, care home closures) and cases of infection in staff and residents. Care home level responses will be linked to individual-level PCR results from the national surveillance whole care home testing data and analysed. Results from the survey are publicly available on the ONS website and have informed government policy on COVID-19 testing in care homes
^9^.

## Methods

### Study design

Prospective cohort study

### Settings

105 care homes in England run by the Four Seasons Health Care (FSHC) group.

### Participants

***Inclusion criteria.*** All residents aged > 65 years and all staff at participating FSHC care home sites; estimated as 11,500 potential participants (5,000 residents and 6,500 staff). Individuals who lack capacity to consent to study participation but have an available consultee can participate. Study materials will be translated into other languages, as necessary, to ensure inclusion of individuals who cannot speak English.

***Exclusion criteria.***
**None**.

### Study schedule

***Baseline assessments and blood sampling (antibody testing and cellular immunity).*** Demographic data and dates of care home entry and exit will be extracted from FSHC systems for all residents and healthcare staff. We will also extract information on care home characteristics (number of beds, residential and nursing care beds, number of patients with dementia, numbers of staff and type, staff turnover, care quality commission (CQC) rating, region, physical layout of the care home, number of visitors, number of suspected and confirmed SARS-CoV-2 cases, number of hospital admissions and deaths). 

Blood samples will be performed for baseline testing of antibody response and cellular immunity in all consenting staff and residents; and from residents who lack capacity provided there is strong justification for this (see section on consent).

***Intensive testing for infection (PCR, antibody testing and cellular immunity) and duration of the antibody and cellular immune response.*** All participants will undergo testing with nasopharyngeal swabs to detect SARS-CoV-2 viral RNA using PCR testing and blood testing to detect antibodies to this virus and cellular immunity. Two further rounds of PCR testing will be repeated at 7–28 day intervals with accompanying symptom data capture. Homes found to have active outbreaks will be prioritised for repeat testing earlier in this window.

Saliva will be collected alongside nasopharyngeal swabs in staff and residents in a subset of 4–8 care homes for PCR testing, to assess saliva as a diagnostic sample type.

Further rounds of blood sampling will be repeated at 6 weeks and 3 months in all participants and at 6 and 12 months in a subset of residents to assess the duration of the antibody response and whether cellular immunity wanes over time.

### Laboratory procedures

Laboratory tests will not be performed by the study team but will be contracted to external laboratories performing these tests as part of their current workload.

All PCR will be performed in national laboratories as part of the national testing programme on clinical isolates from nasopharyngeal swabs. Nasopharyngeal swabs will be carried out by trained care home staff or self-taken according to written instructions. These will be couriered on the same day to the central laboratory who will store them for testing.

PCR testing is performed using an Applied Biosytems 7500 Fast real time PCR system and using the Applied Biosystems TaqPath™ 1-Step Multiplex Master Mix (No ROX) (Cat. A28523) and TaqPath COVID-19-ASY-KIT 1000 (Cat. A47817). Primer sequence details are not currently published. Real time PCR cycling occurs as described in the Applied Biosystems guidelines and involves 1 cycle for 2 minutes at 25°C, 1 cycle for 10 minutes at 53°C, 1 cycle for 2 minutes at 95°C and then 40 cycles of 3 seconds at 95°C and 30 seconds at 60°C. A positive extraction control (Qnostics SARS-CoV-2 Positive Control cat. SCV2PC-075) and negative extraction control (RNAse-free water) is included in each plate. Quantification of the Positive/Negative/Inconclusive status of each sample is determined using the
UgenTec FastFinder Interpretative software.

Blood samples will be collected by trained phlebotomists and will be couriered on the same day to the relevant laboratories for testing and storage.

Antibody tests will be performed using the Abbott
*in vitro* SARS-CoV-2 IgG 6R86 assay using the ARCHITECT diagnostic platform which is widely used across NHS hospitals. These will be carried out in a commercial laboratory who will be contracted by the study team. 

Tests of cellular immunity will be performed on collected blood samples by the University of Birmingham study team using a separate protocol and ethics approval, which will be added to the data repository after it has been finalised.

### Data linkage

We will undertake quarterly data linkage to Hospital Episodes Statistics, Mortality data and virological test results from March 1
^st^ 2020 onwards for all care home residents and staff. The legal basis for accessing identifiable data from all staff and residents without consent is provided through Covid-19: Notice under Regulation 3(4) of the Health Service Control of Patient Information Regulations 2002 (COPI)
^10^. Data linkage will continue for a period of up to 2 years as we anticipate that there will be additional waves of the pandemic in subsequent years.

### Whole genome sequencing

We will collaborate with the COVID-19 Genomics UK Consortium (COG-UK) to sequence viral samples derived from nasopharyngeal swabs from care home staff and residents and link results to epidemiological information (symptoms, dates of infection, admission to hospital, geographical location and care home layout). Sequencing data from care home residents and staff will be compared to sequences derived from hospitals and the community in the region surrounding each care home to make inferences about how SARS-CoV-2 spreads between care homes, the community and hospital settings. We will also explore patterns of transmission within the care home, and whether this varies dependent on whether the index case, as determined by mutations within the sequences and epidemiological data, was symptomatic or asymptomatic, or a member of staff or resident. We will also explore how care home factors such as building layout influence transmission of infection in the care home.

### Qualitative interviews with care home staff

We will undertake in-depth, semi-structured qualitative interviews with 30 care home staff from a sub-sample of participating care homes. This will be done through collaboration with an existing UCL-led study entitled
*COVID-19 Impact and Burden in Care Homes (CATCH-19),* which is funded by the Economic and Social Research Council (ESRC) [ES/V003887/1]
*.* FSHC will identify 6–8 potential care homes for inclusion in this sub-study, considering factors such as care home size, region and the number of COVID-19 cases reported by the care home.

We will use purposive, maximum variation sampling to recruit 3–5 participants per care home, from a range of staff roles (e.g. managers, care assistants, nurses). Interviews will be conducted in the months following the introduction of serological testing (months 2–5 of the study) and will explore the different ways in which the pandemic has impacted on care home staff, residents and ways of working, including: management of suspected or confirmed COVID-19 cases, interaction with other healthcare professionals and settings (e.g. primary and secondary care), access to medicines, advanced care planning, impact on non-COVID-19 care, and staff well-being. The interviews will also focus on how staff interpret and respond to PCR and antibody test results, as well as the subsequent impact on infection prevention control practices and staff behaviours. Specifically, the extent to which care home staff enact personal protective behaviours (i.e. use of PPE, social distancing in the work place)
^11^ and the barriers and enablers to these behaviours. The protocol and topic guide for the qualitative interviews have already been granted ethical approval by the UCL Research Ethics Committee (UCL REC ref: 13355/002) so details are not included in this protocol. 

### Data sources / measurement

The study will include primary data collection, extraction of information from electronic administrative data and linkage to existing medical records. Primary data collection will include nasopharyngeal swabs and saliva for PCR testing; blood samples for antibody testing and storage for analysis of the cellular immune response; data on symptoms of infection to accompany PCR testing; recording of ethnicity; information on care home characteristics and risk factors for infection such as the number of visitors; qualitative interview data.

Data will be extracted from care home records to find out the number of COVID-19 cases, hospital admissions and deaths by care home dating back to March 1
^st^ 2020. Individual-level data will also be extracted for care home residents (age, gender, dates of entry and exit to and from the care home) and for care home staff (dates they started/stopped working at the care home). 

A brief symptom questionnaire will be performed at the time of nasopharyngeal sampling and for the subsequent 7 days to ascertain presence and development of symptoms. This will be performed by the care home manager. The questionnaire is available in the UCL Data Repository (extended data
^12^).

Data linkage will be undertaken in the
NHS Foundry and overseen and quality assured by NHS England.
Figure 1 outlines the data flow for the study.

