### Extended data

UCL Data Repository: COVID-19 in care homes study (VIVALDI) - Symptom questionnaire.xlsx.
https://doi.org/10.5522/04/12764441.v1
^12^

- Symptom record V2 070720.xlsx (Symptom questionnaire administered to all study participants on the day of nasopharyngeal swab (SARS-CoV-2 PCR) that assesses for evidence of current infection)

UCL Data Repository: COVID-19 in care homes (VIVALDI) Statistical analysis plan.
https://doi.org/10.5522/04/12821633.v1
^14^

- VIVALDI analysis plan v1.2 final.pdf (Data analysis plan for VIVALDI-2 study performed by UCL researchers in 105 Four Seasons care homes across England)

UCL Data Repository: CATCH-19 topic guide.
https://doi.org/10.5522/04/12821663.v1
^15^

- CATCH-19_topic guide_V2_02.06.20.docx (Topic guide for CATCH-19 study qualitative interviews to be held with care home staff that are taking part in the VIVALDI study)

Data are available under the terms of the
Creative Commons Attribution 4.0 International license (CC-BY 4.0).

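### Symptom recording has no stated look-back, so people who recovered before a positive swab cannot be told apart from people who never had symptoms

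*Protocol article*

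**What the plan says.** Data sources / measurement sets the symptom window: "A brief symptom questionnaire will be performed at the time of nasopharyngeal sampling and for the subsequent 7 days". The stated aim is to capture both presence and development of symptoms, and the care home manager completes the form. Extended data describes the same form as "Symptom questionnaire administered to all study participants on the day of nasopharyngeal swab (SARS-CoV-2 PCR) that assesses for evidence of current infection". Neither section mentions symptoms before the swab.

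Study schedule sets the swab timing: "Two further rounds of PCR testing will be repeated at 7–28 day intervals with accompanying symptom data capture". It adds: "Homes found to have active outbreaks will be prioritised for repeat testing earlier in this window".

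Three planned uses depend on symptom status. Secondary outcomes lists asymptomatic infection at each swab round, and also a comparison of symptom profiles with the general population. Whole genome sequencing will examine whether transmission differs by whether the index case "was symptomatic or asymptomatic, or a member of staff or resident". The Introduction names the proportion of cases without symptoms as one of the things not accurately known.

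**The concern.** The window looks forward only. If the next swab comes 28 days later, most of the interval has no symptom record, and before the first swab nobody has one. A person can fall ill and recover in that time and still test PCR positive at the swab. That person's record then shows a positive swab with no symptoms on the day or in the following week, exactly like the record of someone who never had symptoms.

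An analysis rule cannot repair this afterwards. The SAP can define asymptomatic infection in any way it likes, but it cannot recover symptoms that nobody asked about. At stake are a named secondary outcome that answers a gap the study set out to fill, and the index-case comparison in the sequencing work. The antibody-based primary outcome is not affected.

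**Working it through.** The plan gives no figure for the asymptomatic proportion or its misclassification, so there is nothing of its own to reproduce here.

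**Step 1: days without symptom recording.** Inputs from the article: recording on day 0 and days 1 to 7 (Data sources / measurement), and a swab gap L of 7 to 28 days (Study schedule). The next record is on day L, so days 8 to L − 1 are uncovered: max(0, L − 8).

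- L = 7: 0 days
- L = 14: 6 days (6/14 = 43% of the interval)
- L = 21: 13 days (13/21 = 62%)
- L = 28: 20 days (20/28 = 71%), or 40 days over two such intervals

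Before round 1 no day is covered in any home.

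**Step 2: other sources.** Data linkage says: "We will undertake quarterly data linkage to Hospital Episodes Statistics, Mortality data and virological test results from March 1". That gives dated test results and admissions, not symptoms. The care home records supply case, admission and death counts by home. The individual fields extracted are age, gender and entry and exit dates for residents, and start and stop dates for staff. None is described as an individual symptom history.

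**Step 3: illustration of size.** The following are assumptions, not figures from the documents: constant incidence; PCR positive from 2 days before symptom onset to P days after it; symptoms lasting D days; no look-back item on the form. A truly symptomatic person who is PCR positive at the swab is missed if onset was more than D days ago (recovered) but after the previous 7-day window closed (less than L − 7 days ago). Hence

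missed share = max(0, min(P, L − 7) − D) / (P + 2).

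At L = 28, L − 7 = 21:

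| Symptom duration D | P = 10 | P = 14 | P = 21 |
|---|---|---|---|
| 7 days | 3/12 = 25% | 7/16 = 44% | 14/23 = 61% |
| 10 days | 0% | 4/16 = 25% | 11/23 = 48% |
| 14 days | 0% | 0% | 7/23 = 30% |

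The share is 0% whenever D is at least P. Shorter illness makes it larger: with D = 3 the row would be 58%, 69% and 78%. With D = 7 the share is 0% at gaps of 7 or 14 days, and 25%, 44% and 30% at 21 days. The formula treats onset before the previous window closed as already captured. At round 2 after a short gap that is optimistic for illness that began before round 1.

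Round 1 has no earlier window, so min(P, L − 7) becomes P. For these values of P the shares equal those in the table, in every home.

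**Step 4: effect on the outcome.** If the true asymptomatic share is a, and PCR positivity lasts equally long in both groups, the reported share is a + (1 − a) × missed share. With a assumed to be 40%, the table's range of 0% to 61% gives 40% up to 0.40 + 0.60 × 0.61 = 77%. Missing past symptoms can only move this share upward.

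**The case against.** The strongest reply is that the form is not shown. The article says when the questionnaire is completed, not what period its questions cover, and a form completed at the swab could ask about preceding days. Nor does the article define asymptomatic infection; the SAP may. A reader might infer that recovered people will be counted as asymptomatic. The documents do not say so, and the inference needs both a form without a look-back and a definition that ignores earlier linked results. It also concerns only people still PCR positive at the swab; those already negative are missed as acute infections altogether. This part of the reply stands. However, the only window stated is the swab day and what follows, and the form is described as assessing current infection, so a form without look-back is the plain reading.

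Linked virological results could show an earlier dated positive, so that a later swab is not read as a new infection. That helps with dating, but it supplies no symptoms.

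A reader might also infer that the error is greater in homes without outbreaks, because outbreak homes are retested sooner. In rounds 2 and 3 the gap does depend on outbreak status. But the article only gives such homes priority within the window, not a 7-day versus 28-day contrast; round 1 affects all homes alike; and homes late in an outbreak may hold more recovered people who are still positive. The documents fix no net direction.

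Finally, a reader might see a contradiction between Data sources / measurement and Extended data about the 7 follow-up days. The latter is a one-line file description and does not deny follow-up, so there is no conflict.

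**Conclusion.** The concern holds as a gap in stated data collection. Up to 20 days per interval, and all time before round 1, have no stated symptom recording, and no other described source fills them. Followed as written, the plan cannot separate post-symptomatic positives from people who never had symptoms, so the asymptomatic-infection outcome and the index-case comparison may be biased towards asymptomatic.

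The day counts follow directly from the article. The size of the bias does not. At a 28-day gap roughly 0% to 60% of truly symptomatic positives are missed, for symptoms of 7 to 14 days and PCR positivity of 10 to 21 days after onset. It is zero when symptoms last as long as positivity and higher if illness is shorter than assumed. No single figure should be quoted as the expected bias, and no claim about outbreak versus other homes should be made beyond the fact that the gap differs in rounds 2 and 3. The point should be addressed, but it concerns secondary analyses.

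**What to change.** Add one item to the existing questionnaire: any listed symptom, with onset date, since the previous study swab or, at round 1, within a fixed and stated period before the swab. If the form already contains such an item, say so in Data sources / measurement.

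Define asymptomatic infection as a positive PCR with no symptom in the look-back, on the swab day or in the following 7 days. Report positives with only earlier symptoms as post-symptomatic, and those with only later onset as pre-symptomatic. Use the same classes for index cases in the sequencing analysis.

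For rounds already completed without the item, report the asymptomatic proportion as an upper bound as far as missed earlier symptoms are concerned.

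The cost is one question and one outcome definition. The downside is some recall error over as much as 28 days, mainly in residents with dementia. Care notes might help, but individual notes are not among the sources the article lists, so using them would add a data source. Recruitment had already started (Study status), so rounds before and after the change should be reported separately.
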